## 10. Socio-Economic Evaluation

Economic inquiries will evaluate the potential economic feasibility of the alternative treatment strategies and potential household impact. Inquiries will focus on COUNTDOWN and household expenditures. The societal perspective will be used to identify and measure resource use for both of the intervention components. An economic evaluation study methodology will be used that includes the identification, measurement, valuation of resource use, and calculation of costs (direct cost, indirect costs, and productivity loss). Cost-effectiveness analysis, cost-benefit analysis, and household impact will be used in the economic evaluation of the studies. 

## 11. Eligibility Criteria and Justification

Community members must reside within the identified villages, to reduce the contamination of people joining in the study units whom have not received the intervention. Individuals who do not have a signed consent form, are acutely unwell, school-enrolled children, and people who indicate that they have had deworming treatment within previous 12 months, will be excluded from parasitological analyses. Children aged less than one year will be excluded. For ALB only, women in their first trimester of pregnancy will be excluded, as it is not recommended to be taken. Its safety during second and third trimesters of pregnancy has been agreed [38].

PZQ and ALB treatments will be provided in accordance with WHO guidelines [12,39], following discussion and consent; the team will ensure no one is coerced into taking part. For ALB, standard screening questions, including an estimate of gestation period, are included on the participant register. Where there may be doubt about pregnancy, ALB will not be administered. Preschool-aged children will not be treated without a parent/guardian being present. School-enrolled children will receive annual MDA at school, and therefore do not need to be included for treatment or parasitological analysis.

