In Ghana, annual MDA is well-established and political motivation high, making it an excellent site in which to research concentrated treatment strategies. Implementation research will explore the feasibility and acceptability of expanding treatment to preschool-age children, out-of-school (school-aged) children, and adults, including pregnant women in selected community sites. The aim is to demonstrate that PZQ and ALB treatments are needed and can be up-scaled and delivered to these demographical groups (which, particularly for PZQ, are not presently targeted within national control programmes), achieving adequate treatment coverage, and resulting in more rapid declines in infection and disease state than annual school-based treatment. Research components include epidemiological, parasitological, social science, and health economics analyses, conducted across an international, multi-stakeholder environment. This study is anticipated to reduce prevalence and intensity of infection of schistosomiasis and STH, increase treatment coverage, and provide evidence to ensure more equitable access to vulnerable groups. In turn, this will help to strengthen the broader health system and generate evidence for improved availability, acceptability, affordability, and accessibility of these NTD interventions to individuals and communities. 

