## 3. Study Area and Site Selection

Due to the highly spatially focal nature of schistosomiasis, regions have been purposively selected according to known endemicity (based on National NTD Control Programme data). Communities within these regions have been selected based on prevalence of at least 10% of schistosomiasis infection (being *S. mansoni* or *S. haematobium*, or both), and proximity to water bodies containing intermediate snail hosts that has previously been ascertained ([name] unpublished). Typically, STH are co-endemic with schistosomiasis in these regions, but are not the basis for site selection, which is the focused on a peri-urban setting surrounding a manmade reservoir. In Ghana, most health care is provided by the government and is largely administered by the Ministry of Health and Ghana Health Service (GHS). There are five levels of health care provision: health posts, health centres and clinics, district hospitals, regional hospitals, and tertiary hospitals. Administratively, GHS is organized at national, regional, and district levels [33]. There are 110 health districts. For Ghana, three communities were selected in Ga South District (Greater Accra Region) (Figure 1). Due to the highly focal nature of disease, we will use routine data collected by GHS and CSIR to serve as controls.

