## 4. Study Design

This longitudinal study will comprise baseline and follow-up surveying of the same individuals. Baseline surveying will involve screening urine and stool samples from a random selection of participants to assess infection prevalence and intensity, and conducting questionnaires to determine associations with WASH and morbidity from both schistosomiasis and STH. Qualitative focus group discussions and in-depth interviews will be held with community members and key informants to assess the understanding of the current MDA strategy, its strengths, and weaknesses, and to identify the feasibility and acceptability of expanding treatment in communities. Comparisons will be made: (i) after 6, 12, and 18 months; and, (ii) to the provision of annual MDA in the regular National School-Based Deworming Programme in schools in the same health districts, at the same time points as a means of comparison to the existing school-based deworming programme in similar prevalence settings. Drug treatment coverage for each survey will also be measured.

This study will involve expanding access to PZQ+ALB treatment for the broader population, including preschool-aged children, out-of-school school-aged children, and adults, including pregnant women. An annual community-based PZQ+ALB treatment will be provided by community health nurses and trained field staff, with cross-checking of enrolled school-aged children so as not to double-up treatments that have been provided in school-based MDA. Treatment will be provided at baseline and 12 months, and the associated reductions in prevalence and intensity of schistosomiasis and STH will be assessed (Figure 2). Parasitological examinations and questionnaires will be conducted on a random sample of participants to determine associations with morbidity from both schistosomiasis and STH, and investigate the feasibility of scale-up. An experienced and trained social science team will conduct qualitative interviews with teachers that are involved in administering annual MDA, and focus group discussions with purposively selected groups of participants by gender, age, and socio-economic status, as well as parents and caregivers.

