For comparison purposes, three school-based sites in the same health districts as the study sites will be selected. In these schools, a random sample of school-aged children who currently receive annual MDA will be selected to participate in parasitological examinations and questionnaires, to enable comparison to the national school-based deworming programme. These data and treatment coverage data, available from the national NTD Control Programme, will be analysed for schools in the same health districts that are not included in the surveys. Due to ethical concerns about conducting parasitological testing for schistosomiasis in communities without the provision of treatment, and where there is no existing opportunity for treatment referral, community sites will not be used for comparison purposes in these studies. This is supported by school sites being the existing MDA unit.

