## 6. Individual Random Selection for Parasitological Examinations and Questionnaires

The study is an augmentation to the current standard of care (annual school-based MDA). With a longitudinal study design, random selection is only required at the individual level for parasitological and epidemiological investigations; all of the individuals in the community will be offered treatment. In each community, following sensitisation, households will be enumerated, with approximate number of residents recorded. Based on the number of households and indicative number of residents in each community, households will then be randomly selected according to a process of selecting every other (odd number houses) household to achieve the sample size. Where a household, or an individual within a household refuses, or is absent during the study, the household will be replaced by the next enumerated household. All the residents within the selected households will be requested to provide urine and stool specimens, and to complete questionnaires. At this stage, individual consent will be elicited, with age, sex, and school-attending status recorded and a unique participant identification number allocated. Selection will proceed until the minimum sample size is achieved. All community members will be invited to receive treatment, with additional consent elicitation by field staff. Treatments will be directly observed, and treatment coverage data will be recorded for all individuals.

For comparison to annual school-based MDA, a junior school (comprising children aged 6–14 years in classes 1 to junior high 3) will be selected at the time the national NTD Control Programme visit occurs. Prior to the deworming, school directors and class teachers will be asked to prepare class lists with the name, age, and sex of the children. Class lists will be imported into Microsoft Excel and each individual will be assigned a computer-generated random number. Individuals will then be selected by study investigators in ascending number order. Individuals who are not present on the day will be replaced by the next individual on the list, until the minimum sample size for parasitological testing is achieved.

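### The school comparison cannot show that community treatment gives faster declines, because no enrolment group is sampled on both sides

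*Protocol article*

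**What the plan says.** **Comparative aim.** The Background says the study should demonstrate expanded treatment "resulting in more rapid declines in infection and disease state than annual school-based treatment". Study Design (section 4) lists the national school-based programme as its second comparison, and for this "three school-based sites in the same health districts as the study sites will be selected".

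**Community sample.** Section 4 describes the target population as "including preschool-aged children, out-of-school school-aged children, and adults, including pregnant women". Section 11 adds two exclusions. The first is enrolment: "School-enrolled children will receive annual MDA at school, and therefore do not need to be included for treatment or parasitological analysis". The second is recent treatment: "people who indicate that they have had deworming treatment within previous 12 months, will be excluded from parasitological analyses". Yet section 6 says "All the residents within the selected households will be requested to provide urine and stool specimens", and Data Analysis (section 14) lists school children among its age ranges.

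**School sample.** Sections 4 and 6 draw it at random from pupils aged 6–14 who are on annual school MDA.

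**Timing.** Section 4 says the school comparison uses the same survey times as the community. Section 6 says the school "will be selected at the time the national NTD Control Programme visit occurs", with class lists drawn up ahead of the deworming.

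**Control source.** Section 3 says "we will use routine data collected by GHS and CSIR to serve as controls". Section 4 relies on the surveyed schools, supplemented by programme data from unsurveyed schools in the same districts.

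**The concern.** To attribute a difference in decline to the treatment strategy, the two groups must be comparable in whatever else drives the decline, or must at least share a stratum in which they can be compared. Here the rule that admits a person to one sample bars that person from the other.

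Treatment history differs as well. The Background describes annual MDA in Ghana as well established and the expanded groups as not presently targeted, particularly for praziquantel. A group at its first round may fall more steeply than pupils who have been through several, even if the two strategies work equally well.

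What is at stake is the conclusion. The Discussion (section 16) intends the results to inform national and WHO policy. A statement that community treatment beats the current school programme would rest on a contrast that cannot isolate strategy.

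**Working it through.** **1. The plan's own figures.** Both sample sizes in section 15 reproduce.

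- Baseline: n = N z² p q / (E²(N − 1) + z² p q), with N = 1500, p = 0.2, q = 0.8, E = 0.03, z = 1.96. This is 921.98 / (1.3491 + 0.6147) = 469.5, rounded up to 470. Then 470 × 1.4 = 658, and 658 × 3 = 1974.
- Follow-up: n = 7.85 × [0.2 × 0.8 + 0.1 × 0.9] / (0.2 − 0.1)² = 7.85 × 0.25 / 0.01 = 196.25. Then 196.25 × 1.6 = 314, and 314 × 3 = 942.

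The inputs are one community prevalence before treatment (20%) and one after (10%). No school term enters either formula.

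**2. The two samples side by side.**

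| | Community survey | School survey |
|---|---|---|
| Enrolled in school | excluded (section 11) | all (sections 4, 6) |
| Age | preschool, out-of-school school-aged, adults (section 4) | 6–14 (section 6) |
| Treatment history | none in the previous 12 months, read as an entry criterion (section 11) | on annual MDA (section 4) |

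Overlap by enrolment is nil. Overlap by age exists at 6–14, but there every community child is out of school and every comparison child is enrolled. Adjusting for age therefore leaves group and enrolment inseparable. Section 5 words the treatment exclusion more softly, as enrolled children who received MDA, but those are the children the school survey samples.

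**3. Timing.** Community treatment is given at baseline and 12 months (section 4), after samples are collected (section 5). The 6- and 18-month surveys thus fall 6 months after a dose, and the 12-month survey about 12 months after one. If section 6 fixes school sampling just before the annual school round, pupils are about 12 months from their last dose. The groups then differ at 6 and 18 months and can match at 12. If section 4 governs, pupils' time since treatment depends on a programme date the article does not give.

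Illustration, for the section 6 reading only. Assume identical strategies, a fall from 20% to 10% after treatment, and a share r of that fall regained linearly by 12 months. Prevalence is 10 + 5r % at 6 months and 10 + 10r % at 12 months, so the false advantage is 5r points: 0 at r = 0, 1.25 at r = 0.25, 2.5 at r = 0.5, 5 at r = 1. The values of r are assumptions.

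**4. What a comparison of declines would need.** Assume independent samples, both groups starting at 20%, the community falling to 10% and schools to x. Ignore household and school clustering. Then n per group and time point = 7.849 × [0.16 + 0.09 + 0.16 + x(1 − x)] / (x − 0.10)².

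| School endpoint x | n per group and time | Power with 942 per group |
|---|---|---|
| 18% | 684 | 91% |
| 16% | 1187 | 70% |
| 15% | 1688 | 55% |
| 14% | 2602 | 39% |

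The school declines, and 942 as a school sample size, are assumptions. The table shows only that the community sample size cannot be taken as powering this comparison. A larger sample would not cure step 2.

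**The case against.** The best defence is that the school comparison is secondary. The primary outcome (section 13), the regression model (section 14) and the sample size (section 15) all concern change within communities. None of the specific objectives in section 2 names a school comparison, and no superiority test is specified. Section 4 also gives an ethical reason for having no community comparator and notes that schools are the existing unit of MDA. All of this stands, and it limits the point to what may be concluded from the school data.

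Several stronger readings are tempting, but the documents do not support them:

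- *That the samples differ in time since treatment by 6 versus 12 months.* This is an inference from section 6, which conflicts with section 4, and it need not apply at 12 months.
- *That the comparison is completely confounded with age.* Out-of-school children aged 6–14 are eligible for the community survey. The age mix differs, but the complete separation is by enrolment.
- *That the primary model contains only time.* It also has age, gender, socioeconomic status, household covariates and interactions of time with sex, age and community.
- *That comparison schools draw pupils from the treated communities.* The article is silent on catchment, and a condensed article may leave that to the full protocol.
- *That there are three rival controls.* The single junior school in section 6 can be read as one per site, which fits section 4. Routine data may complement the surveyed schools. The article should still say which source serves as the control.

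**Conclusion.** The point holds for the comparative claim. As designed, a difference in decline between the community and school samples cannot be attributed to strategy, because strategy coincides with enrolment and treatment history. This follows from sections 4, 6 and 11 alone and needs no assumption about reinfection or timing. The timing effect is conditional on section 6 governing; under the assumed regain it ranges from 0 to 5 percentage points at the 6- and 18-month surveys.

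A reader might infer that the trial's main result is compromised. It is not: the within-community primary outcome, its model and its sample size stand apart from the school data.

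**What to change.** 1. In the Background, remove the claim of faster decline than under annual school-based treatment. In section 4, label the school comparison descriptive. Limit effectiveness conclusions to within-community change.
2. Reconcile section 4 with section 6 on when schools are sampled, and report time since last treatment for both groups at each survey.
3. Reconcile section 3 with section 4 on which data serve as the control.
4. Reconcile the request for specimens from all residents (section 6) with the exclusion in section 11. State whether the school-children age range in section 14 means out-of-school children only.

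These are wording changes, apart from recording time since treatment. The price is a narrower claim.

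Surveying school-enrolled residents of selected households is optional and only a partial remedy. It would change who is surveyed, not who is treated. It would need the 12-month deworming exclusion in section 11 relaxed for that stratum, and it would add to or displace the planned 658 and 314 per site. Because enrolled children on both sides receive the same school MDA, it would estimate only the indirect effect of treating other community members.

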## 12. Sensitisation and Recruitment

Key programme and academic personnel have been involved in the study and its design since inception. These staff will coordinate the selection of sites and subsequently contact key local persons, including district health and education personnel, school and community leaders. A team leader will be assigned to each field team. Following site selection, team leaders will have primary responsibility for correct sensitization of communities, in accordance with established protocols and etiquettes (for example, contact via chiefs prior to community consultation). Recruitment of participants will be via community consultation, with enrolment of all consenting randomly selected households. Recruitment of school children for parasitological comparison will be via teachers, with take-home consent forms and accompanying information sheets being issued for parental consent. Children randomly selected for parasitological surveillance and questionnaires will be given sample pots for stool and urine samples and asked to bring them back the following day. To recruit participants for the focus group discussions and semi-structured interviews, a sampling frame of all of the eligible participants will be obtained. In line with the theory and practice of qualitative research, a purposive sample will then be taken within this study aiming to ensure maximum variation in age, gender, and socio-economic status, pregnancy, and involvement or otherwise in previous school-based distribution. Qualitative data will be collected until reaching the saturation point (when the research team are confident they have received the full range of experiences and responses) [40].

## 13. Outcomes

The primary outcome is the reduction of prevalence of infection of *S. haematobium* and/or *S. mansoni* from the MDA intervention at study endpoint. For purposes of sample size calculations, a 50% reduction in prevalence has been anticipated (i.e., from 20% to 10% after 12 months). As there are negligible existing studies reporting reductions in prevalence of schistosomiasis following community-based treatment, this number has been based on a drug efficacy study of PZQ syrup administered to preschool-aged children, where the reported cure rate against *S. mansoni* was 50.6% [38].

Secondary outcomes to be measured are:(i)To quantify the infection of *S. haematobium*, *S. mansoni* and STH in preschool-aged children, out-of-school children, and adults, including pregnant women;(ii)To assess reductions in intensity of infection of *S. haematobium* and/or *S. mansoni* in study sites at the final timepoint;(iii)To assess reductions in prevalence and intensity of infection of STH in study sites at the final timepoint;(iv)To assess treatment coverage at each timepoint;(v)To investigate associations between the interventions and morbidity, WASH, and demographic factors from the questionnaires; (vi)To assess access of the interventions in the study sites by participants and critical success factors for future implementation, via qualitative assessment;(vii)To investigate the cost-effectiveness of the interventions and household equity impact by detailed examination of the resource use and cost changes of delivery within the study settings.

## 14. Data Analysis

The primary outcome for all sites will be assessed in terms of treatment coverage and reductions in infection prevalence. Secondary outcomes, primarily assessment of morbidity, and demographic factors from the questionnaires and qualitative focus interviews, will also be assessed throughout the study and at the end point. Prevalence and intensity of *S. haematobium*, *S. mansoni* and STH infection will be determined by parasitological methods, according to WHO guidelines [39]. In general, the demographic data will be presented as the mean, median, SD and range for continuous data, and number and proportion of subjects in each category for categorical data. For the intensity of infections we will present overall arithmetic means and subsequently arithmetic means, stratified by gender, age-ranges (pre-school children, school-children, adults), and community at each time point. We will also calculate number and proportion of subjects in each class of intensity at each time point. Finally, for the general health data (i.e., morbidity indicators), we will present number and proportion of subjects at each assessment.

More precisely, the analysis of the primary outcome will be as follows: initially descriptive analysis for overall schistosomiasis (urinary or intestinal) prevalence will be presented per time. If the prevalence is more than 5%, descriptive results will also be presented by gender, age-ranges (pre-school children, school-children, adults), and community per time. Adjusted analysis taking into account the nested structure of the data: repeated measurements within study participants within households will be performed through population average logistic regression models that typically use generalized estimating equations (GEE) [41]. Such models will produce an estimate of the log(odds ratio) that compares the average prevalence of infection (averaged across all clusters: individuals within households) at each time point (i.e., time will be included as a covariate) controlling at the same time for individual—(i.e., age, gender and socioeconomic status as derived from socioeconomic variables included in the questionnaires), as well as household-level covariates [42]. Age, gender, and socioeconomic status are also likely confounders, and thus will be tested in the models. In these models, two-way interactions of time with sex, age, and communities will be considered to explore differences in prevalence rates between different groups. Missing data will be handled through multiple imputation or weighted GEE [43,44].

For the secondary outcomes defined as reductions in prevalence of STHs, we will follow a similar approach as the one outlined above for schistosomiasis, and separately for each of the three STH parasites; we will proceed with GEE models if overall prevalence levels were estimated from the descriptive analysis to be above 5% at baseline in each of those. Subsequently, to assess reductions in the different WHO categories of intensities of schistosomiasis and STHs infections, we will employ similar reasoning for different multinomial GEE models for each of these parasites. For the baseline associations between intensities of infection and morbidity indicators, we will consider different multinomial GEE models for each of the examined parasites (i.e., schistosomiasis and STHs). For the baseline associations between prevalence of infection and WASH indicators, we will consider different logistic GEE models for each of the examined parasites (i.e., schistosomiasis and STHs). All analyses will be conducted using SAS version 9.4 for Windows (SAS Institute Inc., Cary, NC, USA). In all of the models mentioned above, the final retained explanatory variables will be based on information criteria between different fitted models (whenever those are available) and Wald tests. Spatial analysis may be employed to create visual prevalence and/or risk maps of schistosomiasis and STH in the study areas (STATA, R, and QGIS/ArcGIS). For schistosomiasis, at the household level, scatter-plots and semi-variograms will be produced to investigate the relationships between household location and proximity of the shoreline. For qualitative analyses, semi-structured interviews and focus group discussions will be analysed using the framework approach [33]. This approach allows for both deductive and inductive theme identification, through two main phases consisting of five steps:

Phase 1: Data managementStep 1: Familiarisation- the analysis team will read and re-read the verbatim transcripts to ‘familiarise’ themselves with the data and take note of key themes emerging.Step 2: Developing a thematic/coding framework through which to sort the data based on original aims and objectives, and any inductive themes identified during familiarization.Step 3: Indexing/coding data- the thematic/coding framework will be applied to all the data using NVIVO software, Microsoft Word or Excel.

Phase 2: Data explanationStep 4: Charting-data will be lifted from its original context based on its allocation to the coding/thematic framework and placed within a chart.Step 5: Mapping variables at household level.

An economic study of NTDs will be conducted under this umbrella protocol and will be published in a separate protocol paper (in submission). The economic study will involve two research questions. The first will focus on the health equity impact of NTDs and MDAs. The focus will be on the impact of schistosomiasis and STH on household socioeconomic variables, such as education and labour market participation. There will also be a focus on the impact of MDAs on health inequalities. The second research question will focus on the cost-effectiveness and value for money of current MDAs and the proposed health intervention. There will be a baseline and a follow-up assessment of the consequences of the interventions. The outcomes of interest include life-years gained, number of symptom days averted, and number of disabilities and deaths averted. The monetary benefits of the proposed intervention will also be estimated. There will be a focus on the impact of the interventions on labour market productivity and outcomes. Costs will be estimated using a combination of both macro- and micro-costing techniques. Direct costs of deworming drugs, logistics and transportation, storage of resources, materials required for preparation and administration of the drugs, screening and diagnosis, number of people tested per diagnostic technique, treatment, materials and equipment for field workers, payment and training of field workers will be estimated. Given that a societal perspective is being adopted, the costs to households will also be estimated. This will include labour market and educational costs. Time spent in receiving diagnosis and treatment will be estimated. Absenteeism from daily activities due to participation in the health intervention will also be estimated.

This series of analyses will enable the simultaneous identification and potential linkage of the epidemiological, parasitological, sociological, gender, and economic factors that are required to determine the effectiveness of scaling-up of MDA against these parasites. These data will be triangulated to assess all implications, contributing to an integrated, holistic approach to health systems strengthening. 

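### The stated primary model estimates change over time in treated communities only, so it cannot support attributing the reduction to the MDA intervention or a claim of faster decline than school-based treatment

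*Protocol article*

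**What the plan says.** **The claims.** Section 13 defines the primary outcome as a reduction in *Schistosoma* prevalence "from the MDA intervention at study endpoint". Section 1 gives the aim as showing that treatment can be extended to groups outside school, "resulting in more rapid declines in infection and disease state than annual school-based treatment".

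**The planned comparison.** Section 4 lists two comparisons. The first is across 6, 12 and 18 months. The second is "to the provision of annual MDA in the regular National School-Based Deworming Programme in schools in the same health districts", made "at the same time points as a means of comparison to the existing school-based deworming programme in similar prevalence settings". For this, "three school-based sites in the same health districts as the study sites will be selected". Section 3 adds that routine GHS and CSIR data will act as controls.

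**The model.** Section 14 introduces its account as the precise analysis of the primary outcome. It gives descriptive prevalence per survey, then a logistic GEE for repeated measurements on participants within households, comparing average prevalence "at each time point (i.e., time will be included as a covariate"). Adjustment is for age, gender, socioeconomic status and household covariates. On effect modification, "two-way interactions of time with sex, age, and communities will be considered". Neither the school sites nor the routine data appear in any model.

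**The size.** Section 15 sizes follow-up for a fall from 20% at baseline to 10% at follow-up, giving 314 per site and 942 over three sites.

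**The concern.** The time coefficient tests whether prevalence in the surveyed communities is the same at different surveys. That is a sound question, but a positive answer does not say what caused the change or how it compares with the existing programme.

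The design gives reasons why prevalence might move for other causes. School-based MDA continues alongside the study (sections 4, 6 and 11) and may affect transmission. The 18-month survey also falls half a year out of season relative to baseline.

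The time-by-community interaction does not help, because every community in the model receives the intervention. A significant time coefficient could therefore be reported as an effect of expanded treatment, and carried into the national and WHO policy use foreseen in section 16, without the school surveys having entered any test.

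**Working it through.** **1. The plan's own sizes (section 15).**

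- Follow-up: 7.85 × [0.2×0.8 + 0.1×0.9] / 0.1² = 7.85 × 0.25 / 0.01 = 196.25. With the 60% buffer, 196.25 × 1.6 = 314.0, as stated. Three sites give 942.
- Baseline: the finite-population formula with N = 1500, p = 0.2 and E = 0.03 gives 469.5. With the 40% buffer this is 657.3, against 658 stated.

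Both reproduce. The follow-up size concerns one group at two times, and no comparator prevalence enters it.

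**2. How often the time test is significant with no intervention effect.**

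Suppose prevalence falls from p0 = 0.20 to p1 for reasons unrelated to expansion. A two-sided 5% test of the paired change stands in for the baseline-to-endpoint time coefficient:

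- SE = √{[p0q0 + p1q1 − 2ρ√(p0q0p1q1)] × D / n}, where q = 1 − p
- rejection probability = Φ(d/SE − 1.96) + Φ(−d/SE − 1.96), where d = p0 − p1

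The article gives neither the within-person correlation ρ nor the design effect D, so ρ is varied from 0 to 0.5 and D from 1 to 2. The background fall is assumed too.

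Worked case with n = 942, p1 = 0.16, ρ = 0 and D = 1 (the independence variance of the plan's own formula): SE = √(0.2944/942) = 0.0177, d/SE = 2.26, rejection 62%.

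| Background change | n = 942 | one site, n = 314 |
|---|---|---|
| none | 5% | 5% |
| 20% to 18% | 12% to 35% | 7% to 15% |
| 20% to 16% | 36% to 89% | 15% to 45% |
| 20% to 15% | 53% to 98% | 22% to 64% |

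The low end is ρ = 0 with D = 2, and the high end is ρ = 0.5 with D = 1.

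**3. What a comparison of declines would need.**

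The section 15 formula is extended to a difference between two declines, with independent samples, 20% at baseline in both groups, community falling to 10%, and no buffer. Here c is the comparator's follow-up prevalence:

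n per group per time point = 7.85 × [0.16 + 0.09 + 0.16 + c(1 − c)] / (0.10 − (0.20 − c))²

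- Flat comparator (c = 0.20): 7.85 × 0.57 / 0.01 = 447.45, about 448
- c = 0.18: about 684
- c = 0.16: about 1,188
- c = 0.15: about 1,688

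The matching before-after figure is 196. Pooled over three sites, the community side has 942. The article states no school sample size.

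**4. Whether the school sample is a counterfactual.**

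Section 11 excludes school-enrolled children, and people dewormed in the previous 12 months, from community parasitology. Sections 4 and 6 draw the school sample from enrolled children (6 to 14 years) who receive annual MDA. The two samples differ in population, and both are treated.

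**The case against.** The best defence is that the primary outcome is simply before-after. The abstract describes endpoint prevalence from longitudinal surveys, the second objective in section 2 is to assess reduction in prevalence, and section 15 uses a matched-proportions formula. The GEE answers that question. Faster decline than school-based treatment is an aim in section 1, not the primary outcome, and no section states a null hypothesis that the decline is no larger than under the school programme. This stands. The rejection rates above are therefore not type I error of the plan's own test. They are its power to detect a real change that the intervention did not cause.

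A second defence is that the comparison is planned in section 4, that section 4 also gives an ethical reason for having no community comparator, and that a condensed article may leave the comparison's model to another document. This also stands. The missing model is not in itself an error. The problem is that section 14 does fix the primary analysis, and that analysis cannot carry the attribution in section 13 or the comparative claim in section 1.

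Two stronger readings are tempting. A reader might infer that the time test rejects for any background decline. It does not: the probability depends on the size of the fall and is modest for two points. A reader might also infer that adding a programme-by-time term to the primary model would estimate the effect of expansion. It would not. Treated schoolchildren do not show what would have happened to community members left without expanded access, and equal declines in the two samples could mean only that treatment works equally well in both.

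**Conclusion.** The point holds as a mismatch between the claim and the analysis. The stated model is adequate for change in prevalence after MDA and is consistent with the sample size. It cannot separate the intervention from background change, and it says nothing about decline relative to school-based treatment.

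If prevalence would have fallen anyway from 20% to 18%, a significant result with no intervention effect has a probability of about 12% to 35% with 942 followed. For a fall to 16% it is about 36% to 89%. These figures rest on an assumed trend, correlation and design effect, and on a normal approximation in place of the adjusted GEE. They show that the issue can matter, not that such a trend exists. The documents do not show that the before-after test is invalid or that no comparator was planned.

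**What to change.** - **Section 13:** define the primary outcome as change in prevalence of *S. haematobium* and/or *S. mansoni* after the MDA intervention, without attributing the change to it.
- **Section 14:** state that the time coefficient is a before-after change in the treated communities, and not an effect of expanded over school-based treatment.
- **Section 14:** allow a statement about faster decline only from a separate programme-by-time contrast (community against school surveys at the same time points), reported with its confidence interval. Label it secondary and not like-for-like, because enrolled children are excluded from the community parasitology sample and are themselves treated. Do not use it as the estimate of the effect of expansion.

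The cost is wording and one secondary analysis of surveys already planned. The primary claim becomes more modest. The comparative estimate may be imprecise, because no school size is stated and section 15 does not size the study for it: about 448 per group per time point before any buffer, even against a flat comparator, and more if the comparator also declines.
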